## Abstract

**Background:**

Antipsychotic drug-induced weight gain puts individuals with schizophrenia at increased cardiometabolic risk. As a potential intervention for this problem, we describe the theoretical background and a protocol for a feasibility randomised controlled trial (RCT) of approach bias modification (ABM) training combined with real versus sham (placebo) transcranial direct current stimulation (tDCS). The primary aim of this trial is to obtain information that will guide decision making and protocol development in relation to a future large-scale RCT of ABM and tDCS in this group of participants. Second, the study will assess the preliminary efficacy of ABM + tDCS in reducing food cravings in people who take antipsychotic medication.

**Methods:**

Thirty adults with a DSM-V diagnosis of schizophrenia or schizoaffective disorder treated with anti-psychotic medication will be randomly allocated to receive five sessions that will combine ABM and real or sham tDCS, in a parallel group design. In this feasibility study, a broad range of outcome variables will be examined. Measures will include food craving, psychopathology (e.g. symptoms of schizophrenia and depression), neuropsychological processes (such as attentional bias and impulsiveness), and the tolerability and acceptability of tDCS. The feasibility of conducting a large-scale RCT of ABM + tDCS and appropriateness of tDCS as a treatment for antipsychotic drug-induced weight gain will be evaluated by assessment of recruitment and retention rates, acceptability of random allocation, blinding success (allocation concealment), completion of treatment sessions and research assessments (baseline, post-treatment and follow-up).

**Discussion:**

The effect sizes generated and other findings from this trial will inform a future large-scale RCT with respect to decisions on primary outcome measures and other aspects of protocol development. In addition, results from this study will provide a preliminary indication of the efficacy of ABM + tDCS treatment for antipsychotic drug-induced weight gain.

**Trial registration:**

ISRCTN Registry, ISRCTN13280178. Registered on 16 October 2018.

## Background

Individuals taking antipsychotic medication show increased food craving, caloric intake and weight gain which puts them at elevated risk for obesity-related conditions, e.g. type 2 diabetes and cardiovascular disease [1]. People with schizophrenia have a higher mortality rate than the general population, mainly due to physical illnesses [2]. Reducing the weight-related side effects of antipsychotic medication has the potential to improve health outcomes for this population.

Antipsychotic drug-induced weight gain is well documented. A meta-analysis of 81 studies reported that, after 10 weeks of treatment, there was a mean weight increase of 4.45 kg in patients receiving clozapine and 4.15 kg for those receiving olanzapine [3]. Fountaine et al. [4] showed that olanzapine treatment resulted in an estimated 345 kcal/day (18%) excess energy intake in 30 healthy male volunteers and 2.65 kg increased body weight (over 15 days). Another study showed that four weeks of treatment with olanzapine was associated with an estimated increase of energy intake of 598 kcal/day (28%) in 10 male adolescents [5]. These reports are broadly consistent with another review which concluded that patients with schizophrenia are more likely than matched controls to consume a diet poor in fibre and fruit and rich in saturated fat [6].

Treatments for antipsychotic drug-induced weight gain include medication and behavioural interventions such as nutritional advice, cognitive behavioural therapy and exercise. Pharmacological interventions (e.g. fenfluramine, sibutramine, reboxetine, metformin, topiramate) are not very effective and can have significant side effects [7], whereas research on behavioural interventions has produced mixed results. In a five-year naturalistic study of 82 outpatients newly started on clozapine, weight gain occurred despite active weight loss programmes involving diet and exercise [8]. A meta-analysis of 20 trials of exercise interventions reported no significant effect on body mass index (BMI) [9], whereas a review of 13 studies investigating behavioural interventions reported a weight loss of 3.15% of initial weight, well below the 5%–10% threshold considered sufficient to improve weight-related complications [10]. Another meta-analysis of 17 studies concluded that behavioural interventions prevented and/or reduced antipsychotic-associated weight gain (3.12 kg less weight gain); however, weight was significantly improved only in outpatient trials (*p* < 0.0001) but not in inpatient or mixed samples (*p* = 0.09–0.96) [7]. On the basis of these findings, there is a need for new treatments that target weight gain in people who take antipsychotic medication, especially those who may find it hard to engage in exercise or therapy.

Human and animal studies suggest that antipsychotic drugs stimulate appetite by interacting with dopamine (D2), serotonin (5HT2a & 5HT2c) and histamine (H1, H2) receptors [1]. Changes in peripheral hormones, e.g. leptin, ghrelin and adiponectin, have been reported to be involved [11]. Fat deposition may be facilitated by stress induced activation of the hypothalamic-pituitary-adrenal axis [12]. Genetic predisposition may also play a part, e.g. antipsychotic drug-induced weight gain is reported to be correlated with polymorphisms in the common promoter region for 5HT2c receptors [13] and polymorphisms near the melanocortin 4 receptor gene (MC4R4) [14].

As a result of altered appetite and increased susceptibility to hunger, people taking antipsychotic medication may develop disordered dietary behaviours [15]. Brömel et al. [16] showed that out of 12 patients started on clozapine, nine reported increased appetite and two developed binge-eating episodes. In another study of 74 patients on either olanzapine or clozapine, 37 screened positively for binge eating, with nine fulfilling criteria for binge-eating disorder and five for bulimia nervosa [17]. Additionally, patients who screened positively for binge eating showed higher BMIs and higher BMI gains during treatment. These results suggest that modifying food cravings and/or food consumption may affect antipsychotic drug-induced weight gain.

The observations described above are consistent with evidence from neuroimaging studies. A functional magnetic resonance imaging (fMRI) study of 25 individuals after one week of olanzapine treatment showed enhanced anticipatory and consummatory responses to food rewards and decreased responsivity to food consumption [18]. Another study of 25 individuals after 16 weeks of olanzapine treatment reported increased sensitivity to appetitive stimuli in insular cortices, amygdala and cerebellum, compared with controls [19]. There was also an increased response to appetite-related stimuli from baseline to post treatment, in the frontal cortex, fusiform gyrus, amygdala and insula.

Neural activity in certain brain areas can be enhanced or reduced by neuromodulation procedures, e.g. repetitive transcranial magnetic stimulation (rTMS) and transcranial direct current stimulation (tDCS). These non-invasive brain stimulation methods have demonstrated therapeutic potential in major depressive disorder [20], bipolar affective disorder [21], obsessive compulsive disorder, generalised anxiety disorder and substance use disorder [22]. They have also been trialled and well received in people with schizophrenia, helping to alleviate auditory verbal hallucinations and improving negative symptoms [22].

Brain stimulation may also be a promising tool for reducing food cravings [23] which could be used to treat antipsychotic-induced weight gain. The most common target of neuromodulation is the dorsolateral prefrontal cortex (dlPFC) which has been associated with control of eating via possible mechanisms of reward valuation, attention and inhibitory control [24]. For example, one session of high-frequency rTMS delivered to the left dlPFC lowered cue-induced food cravings in people with bulimic disorder [25, 26] and tDCS applied to the dlPFC reduced food cravings in healthy participants [27, 28] and the desire to eat in overweight and obese participants [29].

Another potential intervention for antipsychotic drug-induced weight gain is approach bias modification (ABM) training. ABM is a computer training aiming to modify implicit approach biases through teaching participants to avoid negative stimuli [30]. A review of 12 meta-analyses concluded that a course of ABM sessions can shift target biases in adults, with moderate effect sizes [31]. ABM can also be effective at re-training approach bias to appetitive cues such food and alcohol [32]. ABM significantly reduced approach tendencies and attention towards food cues in a sample of people who binge eat [33] and reduced eating disorders symptoms in a sample of people with either bulimia nervosa or binge-eating disorder [34].

TDCS has been proposed to modulate neural activity by changing the threshold for discharge of the stimulated neurons [35], i.e. it does not induce changes in neuronal firing in resting neuronal networks. Because tDCS does not alter resting networks, it has been proposed [36] that the potential therapeutic effects of tDCS are likely to be improved by pairing it with the behaviour (and associated changes in neuronal activity) that one is seeking to modify [36] (e.g. bias towards high-calorie foods). In this way, the effects of ABM may be enhanced by tDCS, i.e. it may increase neuroplasticity [37] and potentially aid learning aimed at avoiding high-calorie foods. In fact, this has been reported by Heeren et al. [38], who found that neuromodulation boosted the effects of cognitive training aimed at reducing cognitive bias and improving response inhibition. Den Uyl et al. [39] conducted four sessions of concurrent ABM and tDCS over seven days on alcohol-dependent inpatients. Although no enhanced effect of tDCS on ABM training was found, a reduced probability of relapse at the one-year follow-up was noted in the real tDCS group compared to sham. This indicates that combined tDCS and ABM can potentially have a stronger effect on reducing food cravings than either of the treatments alone.

In summary, research shows that dietary behaviours can be altered by neuromodulation methods as well as ABM training. To our knowledge, this will be the first time that both these interventions will be combined and applied in people taking antipsychotic medication. The proposed feasibility study is a randomised controlled trial (RCT) comparing ABM training combined with real (active) or sham (placebo) anodal tDCS to the right dlPFC in individuals with schizophrenia who take antipsychotic medication. We will assess recruitment, attendance, retention and follow-up rates that will inform the development of a large-scale RCT. Changes to food cravings and eating behaviours as well as other clinical outcomes (e.g. depression, anxiety, impulsiveness, schizophrenia symptoms) will be measured before and after the treatment intervention and at a two-week follow-up.

### Aims

The aims of the present study are to:
establish the feasibility of conducting a large-scale RCT of ABM + tDCS in people with schizophrenia who take antipsychotic medication: this will involve assessing safety (adverse events), recruitment, willingness to undergo random allocation to five sessions of ABM combined with real or sham tDCS, attendance and retention rates;determine the best instruments for measuring outcomes in a future full trial by examining the quality, completeness and variability in the data;estimate the treatment effect sizes and standard deviations for outcome measures to inform the sample size calculation for a large-scale RCT;explore participants’ views on the acceptability, credibility, tolerability and experience of ABM + tDCS.

Based on neuromodulation studies conducted by our group [40, 41] and others [42–44] in people who experience food cravings, we predict that, compared to ABM + sham tDCS treatment, five sessions of ABM + real tDCS applied to the dlPFC will:
decrease approach bias towards food stimuli;decrease state food craving after cue exposure;decrease trait food craving from baseline to post assessment;be considered by patients as an acceptable and useful treatment for antipsychotic drug-induced weight gain.

## Methods

### Design

This is a parallel group, double-blind, two-arm RCT. Participants will be randomly allocated to receive five sessions of either ABM + real tDCS (treatment group) or ABM + sham tDCS (control group) over 3–4 weeks, delivered in addition to treatment as usual. Outcomes will be measured at baseline, after treatment and at the two-week follow-up. Participants in the control group will be offered the opportunity to receive ABM + real tDCS at the end of the study. The protocol is outlined in Fig. 1; Table 1 gives details of assessments and timepoints. Our study design will allow us to establish whether adding tDCS to the ABM is better than ABM alone. Specifically, this will be achieved by administering the Food Approach-Avoidance Task (F-AAT) and the Stimulus Response Compatibility Task (SRC) at baseline and after treatment to measure approach bias towards high-calorie foods in the two groups (real-tDCS and ABM vs sham-tDCS and ABM).

**Fig. 1 Fig1:**
[figure not shown]
Schematic diagram of the study protocol

**Table 1 Tab1:** Study schedule of enrolment, interventions and assessments

	Study period						
	Screen visit (all participants)	Baseline (all participants)	Training: ABM + real tDCS	Training: ABM + sham tDCS	Post-assessment (all participants)	Follow-up (all participants)	Study end (all participants)
Timepoint	–t1	0	t1	t1	t2	t3	t4
Participant information sheet, inclusion /exclusion criteria and tDCS safety screen	X						
Informed consent		X					
Demographic information		X			X		
Questionnaires		X			X		
Food-related tasks		X			X		
Approach bias assessment tasks		X			X		
Pre-ABM + tDCS measures: multiple VASs, blood pressure and pulse			X	X			
Anodal real tDCS to dlPFC			X				
Anodal sham tDCS to dlPFC				X			
Approach bias modification training			X	X			
Post ABM + tDCS measures: multiple VASs, blood pressure and pulse			X	X			
Tolerance, discomfort and side effects of tDCS			X	X			
Acceptability questionnaire					X		
Blinding assessment questionnaire					X		
Follow-up questionnaires						X	
Unblinding							X

*ABM* approach bias modification, *dlPFC* dorsolateral prefrontal cortex, *tDCS* transcranial direct current stimulation, *VAS* visual analogue scale

### Setting

The study will be conducted at the Institute of Psychiatry, Psychology and Neuroscience (IoPPN) and at inpatient and community services at the South London and Maudsley NHS Foundation Trust (SLaM).

### Ethical approval and trial registration

Ethical approval for the study was obtained from the Oxford B Research Ethics Committee (REC; reference no. 19/SW/0095). The study is registered on the International Standard Randomised Controlled Trial Number (ISRCTN) registry (registration no. ISRCTN13280178).

### Participants and recruitment

Participants will be recruited from inpatient and community services at the SLaM, through websites (such as IoPPN), through social media platforms (such as the Eating Disorders Unit’s official Twitter account) and through the Consent 4 Contact SLaM initiative [45]. Participants will be paid £90 for their time and effort.

### Inclusion criteria

Male or female participants will be included if they have a current DSM-V diagnosis of schizophrenia or schizoaffective disorder, are aged 18–65 years and have been on a stable dose of antipsychotic medication for at least six weeks before study enrolment.

### Exclusion criteria

Participants will be excluded if they: suffer from any significant/unstable co-morbid medical or psychiatric disorders (e.g. substance dependence); are on a dose of antidepressant medication that has not been stable for at least six weeks; are allergic to any of the foods used in the study; or cannot understand verbal or written English. A tDCS safety questionnaire will be administered and individuals will be excluded if they: have a history of epileptic seizures, stroke or brain injury; have any implanted metal devices in the head; suffer from frequent or severe headaches or dizziness; are pregnant.

### Sample size

As this is a feasibility study, no a priori sample calculation has been conducted. This study aims to provide effect sizes on which future large-scale studies can be based. Total sample sizes of 24–50 have been recommended for feasibility trials with a primary outcome measured on a continuous scale, mainly because estimates of the standard deviation for normally distributed variables tend to stabilise around this size [46, 47]. We have chosen a total sample size of 30 (which exceeds the lower end recommended for feasibility trials).

### Randomisation

Generation and implementation of the randomisation sequence will be conducted independently from the trial team by a King’s College researcher using Sealed Envelope, an online randomisation tool [48]. Once the baseline assessment has been conducted and the patient is recruited and has consented to the trial, he/she will be allocated to one of the two intervention arms in a ratio of 1:1. Group allocation will be communicated via phone, email or in a sealed non-transparent envelope to the appropriate member of the research team for each participant.

### Intervention

#### Study procedures

In both groups, participants will receive five sessions of ABM + real/sham tDCS over 3–4 weeks. ABM and tDCS will be delivered at the same time, i.e. participants will engage in the ABM while receiving brain stimulation. Each session will last approximately 40 min, including preparation time, 20 min of ABM + tDCS and questionnaire administration. The ABM will start 1 min after the start of the brain stimulation, to allow participants to get used to the brain stimulation. Thereafter, ABM will take place over 15 min and brain stimulation will then continue for a further 4 min. Throughout the study, participants will be able to access or continue treatment as usual as recommended by their treating team.

#### ABM training

The ABM programme is based on a modified version of the Food Approach /Avoidance Task (F-AAT). In the F-AAT task, participants are shown pictures of food and control (i.e. neutral household and office) items. They are required to pull (pictures grow bigger) or push (pictures grow smaller) a joystick in response to the outer frame of the picture (round vs rectangular), irrespective of the picture content. The ABM task adopts an implicit learning paradigm by presenting all food pictures in the ‘push’ (i.e. avoid) format. The study procedure for ABM administration is in accord with a protocol paper [49], with updated images of foods and non-edible objects from a food-pictures database [50].

#### tDCS

TDCS (both real and sham) will be delivered using a neuroConn® DC-STIMULATOR device at a constant current of 2 mA (with a 10-s fade in/out) using two 25 cm^2^ surface sponge electrodes soaked in a sterile saline solution (0.9% sodium chloride). The anode will be placed over the right dlPFC and the cathode over the left dlPFC. The stimulation site will correspond to the F3 location based on the International 10–20 system [51]. In the real tDCS group, current will be delivered for the whole duration of the stimulation (20 min). In the sham (placebo) tDCS group, current will automatically turn off after 30 s.

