#### Safety

Study procedures and parameters are in accord with safety and application guidelines for tDCS [52]. Treatment will be delivered by personnel trained in tDCS administration. A case record form for each trial participant will be kept to monitor session attendance and any side effects or adverse events according to prespecified criteria. Any protocol violations will also be recorded there. To ensure safety, participants’ blood pressure and pulse will be monitored before and after each stimulation. TDCS is generally well-tolerated and is associated with relatively minor side effects. According to the review of 567 tDCS sessions, adverse events (and occurrence rates) included: tingling sensation (70.6%); moderate fatigue (35.3%); light itching sensation under the stimulation electrodes (30.4%); headache (11.8%); nausea (2.9%); and insomnia (0.98%) [53]. Another review of 209 tDCS studies found similar rates of adverse events in both real and sham stimulation groups [54]. In the event of mild side effects (e.g. a slight headache) participants will not be withdrawn but will be able to discontinue tDCS treatment if they wish. TDCS will be immediately halted if the participant experiences a more serious adverse event or if any other indicators of serious medical risk emerge. Treatment will only be restarted if it is deemed safe to continue by a medical professional. Standard King’s College London insurance and NHS indemnity arrangements will apply to this study.

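### The only electrode coordinate given, F3, is on the left, but the active (anodal) target is the right dlPFC

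*Protocol article*

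**What the plan says.** The tDCS section (Methods, Intervention) specifies two surface electrodes and their sides: "The anode will be placed over the right dlPFC and the cathode over the left dlPFC". The next sentence gives the scalp coordinate: "The stimulation site will correspond to the F3 location", with reference to the International 10-20 system. The wording is singular and does not say which electrode is meant. No other coordinate appears in the article.

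The end of the Background describes the randomised comparison as real or sham "anodal tDCS to the right dlPFC in individuals with schizophrenia". Table 1 lists the intervention as "Anodal real tDCS to dlPFC", with a matching row for sham; neither row gives a side.

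**The concern.** Two adjacent sentences point to different sides of the head for the electrode that defines the treatment. The anode is to go on the right, but the one coordinate offered for the stimulation site is on the left. An operator or a later trial team who took that coordinate as the anode position would reverse the montage.

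This matters because real versus sham stimulation is the only thing that differs between the arms. The Discussion paragraph of the Abstract says that the resulting effect sizes will feed into a future large-scale RCT. An effect size is of use to that trial only if it is clear which montage produced it.

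**Working it through.** There is no stated figure to reproduce. The check is one of consistency, followed by a count of the sessions that could be involved.

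**Side of the coordinate.** The 10-20 system, which the protocol itself adopts, labels left-sided positions with odd numbers and right-sided positions with even numbers. F3 is therefore left frontal and F4 is the matching right frontal position.

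**Statements side by side.**

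| Place in the protocol article | Electrode or target | Side |
|---|---|---|
| Background, last paragraph | Anodal stimulation | Right |
| Table 1, two rows (real, sham) | Anodal stimulation | Not given |
| tDCS section, placement sentence | Anode | Right |
| tDCS section, placement sentence | Cathode | Left |
| tDCS section, coordinate sentence | Stimulation site, electrode not named | Left (F3) |

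**Which electrode does the stimulation site mean?**

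- The treatment is named by the anode in 3 places (Background once, Table 1 twice) and by the cathode in 0.
- F3 is given once and F4 not at all.
- If the site is the anode, F3 is on the wrong side.
- If the site is the cathode, F3 is on the right side for that electrode. The anode, which defines the treatment, then has no coordinate, although two electrodes are specified.

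The sentence needs correcting on either reading. The likely explanations are a slip for F4 or a shortened form of anode F4, cathode F3.

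**Sessions that could be involved.**

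- Total sample size: "We have chosen a total sample size of 30" (Sample size).
- Allocation: "allocated to one of the two intervention arms in a ratio of 1:1" (Randomisation).
- Sessions: participants are "randomly allocated to receive five sessions of either" real or sham treatment (Design).
- Participants in the real-tDCS arm: 30 / 2 = 15.
- Planned real-tDCS sessions: 15 × 5 = 75.
- Lower bound: 0 of 75, if operators followed the hemispheres stated in words.
- Upper bound: 75 of 75, if F3 was used for the anode throughout.

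The count assumes an exact even split and full attendance. It leaves out the real tDCS offered to control participants after the study.

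**The case against.** The strongest reply is that the article does not contradict itself outright. The coordinate sentence never says that the anode goes at F3. It follows directly on a statement that the cathode goes on the left, and F3 fits that. On this reading the text is incomplete rather than wrong, and a missing coordinate is an operating detail that a condensed article may leave to the full protocol. An operator would also have to override an explicit instruction naming electrode and hemisphere in order to put the anode on the left, and the Safety section says that trained staff deliver the treatment. The placement applies to both arms, so the real-versus-sham comparison would stay internally valid; only the montage it describes would be in doubt. Finally, feasibility is the primary aim, and a range of 0 to 75 sessions is simply everything possible.

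Much of this stands. The polarity can be recovered from the words, the session range is a bound and not an estimate, and recruitment, retention and attendance are largely unaffected. The Table 1 entries show that the treatment is named by the anode but do not help on side.

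The cathode reading does not rescue the sentence. It does not fit a treatment named throughout by its anode, and it leaves that electrode without a position. Nor is this a detail left to a fuller document: the article does state a coordinate, and the coordinate conflicts with the sentence before it.

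The Safety section offers a partial safeguard. It says "A case record form for each trial participant will be kept to monitor session attendance and any side effects or adverse events", and adds that protocol violations are recorded on the same form. But it does not say that electrode position is recorded, and a violation can be judged only against a clear standard, which is what the two sentences fail to give.

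**Conclusion.** The concern holds. The single coordinate is on the wrong side for the active electrode as the trial defines it, and this error sits in the operative description of the only randomised contrast. The conclusion rests on the 10-20 labelling convention and on reading the stimulation site as the anodal target, which the article's own naming supports.

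The consequence may be no more than a faulty description. The article does not show which montage was delivered, so the number of affected sessions cannot be narrowed within the bounds above. No bias is claimed, and no sample size, randomisation or analysis element changes. The correction should still be made, because the effect sizes are meant to carry forward to a larger trial.

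**What to change.** First have the sponsor confirm that right anodal stimulation is intended. Then:

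1. Replace the coordinate sentence with: *anode at F4 (right dlPFC), cathode at F3 (left dlPFC)*.
2. Make the operator instructions match. This also covers the real tDCS offered to sham participants after the study, which is to follow the same procedure.
3. As recruitment began in June 2019, state in the results report which montage was delivered, as far as operators or available records can confirm it. The case record form may not settle this.

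The cost is one corrected sentence, one check of the operator instructions and one line in the results report. No additional patients, visits or analyses are needed.
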